## Study medication

In case of severe bleeding, the randomised study drug will once be administered. The latter will allow to detect the suggested reduction of the need for blood products.

### Experimental intervention

Wilate® is a 1:1 balanced mixture of von Willebrand factor and coagulation factor VIII. It belongs to the group of anti-haemorrhagic and coagulation factors. It is extracted from plasma, freeze-dried and virus-inactivated by two steps. In Switzerland, it is registered to prevent and treat bleeding of patients suffering from haemophilia A and von Willebrand disease. It is administered as dry solid, which has to be dissolved with the included solvent (water for injection including 0.1% polysorbat 80).

The vWF of the product acts like the vWF of human plasma. It is a key protein mediating platelet adhesion on the surface of damaged endothelial cells or collagen, initiating platelet-platelet aggregation and supporting platelet activation. It plays also an important role in protecting FVIII from early activation and clearance.

The product’s coagulation factor VIII acts in the activated form like the regular factor VIIIa. It takes part in the coagulation amplification by activating factor X to Xa with factor IXa as a co-factor. Activation of factor X generates thrombin from prothrombin.

Wilate® is approved in Switzerland for prophylaxis and treatment of bleeding in patients suffering from von Willebrand disease and haemophilia type A.

In case of haemorrhage and indicated platelet transfusion, a study package will be prepared by an unblinded site member and afterwards provided to the participating patient’s physician in charge with one dose of Wilate® (2000 IU vWF and 2000 IU factor VIII and water for injection including 0.1% polysorbat 80) or placebo (replenished with sodium chloride 0.9%). Additionally, one platelet concentrate provided by the blood bank of the University Hospital of Basel will be ordered. Platelet components are either single donor apheresis or buffy-coat pooled platelet components, pathogen-reduced and containing at least 2.4 × 10e11 platelets per unit.

It is recommended to administer 20–50 IE of Wilate® per kg/BW in vWF patients with acute bleeding. The dosage of Wilate® in this trial will be 2000 IU of vWF and 2000 IU factor VIII each in combination with one or two platelet concentrates. The medication (Wilate® or placebo and platelet concentrates) will be administered intravenously, because this is the only possible route of administration of Wilate® and platelets. The objective of this treatment is to stop the haemorrhage by administering the intervention drug once. Due to the long half-time of the study drug, a single administration will be sufficient for the 48-h observation period, also in cases where further thrombocyte transfusions are needed.

To make sure the study drug will be distributed within the body, a minimum waiting period of 10 min should be met whenever possible and depending on the clinical picture before platelet concentrate transfusion (usually this is the case as platelet concentrates have to be ordered in most situations). A waiting period of 20–30 min would be ideal. Thereafter, the clinical situation should be reassessed and the decision to transfuse a second platelet concentrate be taken after careful consideration.

### Control intervention

The control group will be given placebo together with platelets. Our placebo will be provided by the hospital pharmacy of the University Hospital of Basel. The placebo will be sodium chloride 0.9% from Fresenius. The carton contains two Mini-Plasco with 10 ml each. An unblinded member of the ICU team—independent from the study team—will prepare either Wilate® or placebo in a syringe as described in the instructions, which will be delivered with the kit.

The blinding of the trial medication will be a carton, which includes either Wilate® 2× 1000 UI or placebo (sodium chloride 0.9%, 2 × 10 ml).

## Outcome measures

### Primary outcome measure

The primary outcome measure is the number of fresh frozen plasma (FFP) and red blood cell (RBC) transfusions according to groups.

### Secondary outcome measures

Secondary outcomes will consist of the following:Number of platelet concentrates transfused within the first 48 h after treatment of study medicationQuantity of blood loss in the first 48 h after treatment with the study medicationLength of stay in ICU and hospitalNumber of revision surgeries or secondary interventions (e.g. re-bronchoscopy, re-gastroscopy) for haemorrhage controlMortality in ICU, hospital, 30-day and 1-year

### Other outcome measures

Additional outcomes include the following:Platelet function analysis as assessed by VerifyNow ® ADP testAmount of administered coagulation factors: 4-factor prothrombin complex concentrate, calcium, tranexamic acid, fibrinogen concentrate, coagulation factor XIII concentrate, vitamin K, antithrombin concentrate and recombinant coagulation factor VIIaEstimate of costs for blood transfusion products during ICU stay (see Supplementary Table 1a and b)Thromboembolic complications

### Safety outcome measures

#### Adverse events

An adverse event (AE) is any untoward medical incident in a patient or a clinical investigation participant administered a pharmaceutical product and which does not necessarily have a causal relationship with the study procedure. An AE can therefore be any unfavourable and unintended sign (including an abnormal laboratory finding), symptom or disease temporally associated with the use of a medicinal (investigational) product, whether or not related to the medicinal (investigational) product. [ICH E6 1.2] AEs are therefore difficult to detect in critically ill patients since the physical state leading to ICU admission itself may already lead to severe complications and further deterioration of physical and mental health.

ICU staff will be instructed to pay attention to allergic reactions like exanthema, flushing, urticaria, stridor, bronchospasm, shock and shortness of breath. These observations will be recorded together with the time of onset, duration, cessation, action that were taken, assessment of intensity and its relation to the study treatment. All adverse events will be reported to investigators and recorded by them on the participating patient’s data sheet during their following visits. Other extraordinary or questionable side effects will also be recorded. The occurrence of thromboembolic events will also be registered until the participating patients are discharged from the hospital.

Serious adverse events (SAEs) are classified as any medical occurrence that results in death, is life-threatening, requires prolongation of existing hospitalisation, or results in persistent or significant disability/incapacity. SAE reporting is required from the responsible Swiss authorities. The third criterion from the SAE definition will be excluded in our trial, as the occurrence of severe bleeding generally leads to prolongation of ICU and/or hospital stay.

A serious unexpected adverse drug reaction (SUSAR) indicates an adverse drug reaction that is of a nature or a severity inconsistent with the applicable product information. Transfusion-related side effects will therefore not be declared as SUSAR.

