^g^Including von Willebrand factor ristocetin cofactor (VWF:Rco); factors II, V, and VII; INR; and platelets count and level of thrombin

^h^Beriplex, Cyklokapron, Konakion, Kyberin, Fibrogammin, NovoSeven, ionised calcium, etc. (see Additional file 1: Table S1)

**Table 3 Tab3:** ICU follow-up data to be assessed within the 48-hour study period beginning at study drug administration

	***Metavision®***	RedCap®
Administration of study medication (or placebo)		
Platelet function analysis (VerifyNow® ADP test) 30–60 min after administration of study drug		X
Check if informed consent is possible		X
Amount of blood loss since drug administration		X
Cause of bleeding (if occurred)		X
SOFA score	X	
Vital parameters^a^	X	
Lowest temperature measured^b^		X
Acidosis occurred (pH < 7.35)		X
Duration of acidosis		X
Full blood count^c^	X	
Coagulation laboratory^d^	X	
ROTEM	X	
Level of vWF and FVIII	X	
Haemoglobin concentration	X	
Fluid balance^e^	X	
Number of given RBCs	X	
Number of given FFPs	X	
Number of given platelet concentrates	X	
Amount of Prothromblex after study intervention	X	
Amount of tranexam acid after study intervention	X	
Amount of fibrinogen after study intervention	X	
Name/amount of other given coagulation products^f^	X	
Number of revision surgery for haemorrhage control		X
Transfusion-related side effects (AE, SAE, see 3.7)^g^		X
Thromboembolic events		X
Any recurrent bleeding such as cerebral haemorrhage, DIC		X

^a^Blood pressure, pulse, SpO_2_, ScvO_2_, SvO_2_ and respiratory rate

^b^Lowest temperature measured since ICU admission

^c^Hemoglobin, leucocytes, erythrocites, haematocrit, mean corpuscular volume (MCV), mean corpuscular haemoglobin (MCH), mean corpuscular haemoglobin concentration (MCHC), red cell distribution width (RDW), thrombocytes, quick, international normalised ratio (INR), activated partial thromboplastin time (APTT), thrombin time 1 (TZ1), and fibrinogen^d^ including factors II, V and VII; INR; platelets count; and level of thrombin

^e^Since ICU admission until 48 h after the study drug administration

^f^Beriplex, Cyklokapron, Konakion, Kyberin, Fibrogammin, NovoSeven, ionised calcium, etc. (see above)

^g^48-h observation period

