## Adherence to intervention protocols

Each time a platelet concentrate is prescribed, a red flag will appear in our data monitoring system. The vWF kit from Basel (HemosIL^2^) will be used to measure the vWF activity (vWF:Ac). The vWF:Ac is measured at four individual times per patient: baseline, 30 min after the thrombocyte concentrate administration has ended, the following day at 6 AM and the day after at 6 AM.

Because the study medication is only a few millilitres and should be given at least 5 min before giving platelets, handling it only for a few minutes will be enough to get it to room temperature, so the study medication will be kept in the fridge until randomisation.

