#### Safety analyses

Descriptive analysis and univariate tests will be performed for the number of SAE by severity grade, transfusion-related side effects, recurrent bleeding and the number of thromboembolic events within 48 h after study drug administration.

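### The blanket rule that transfusion-related side effects are never a SUSAR does not follow from the SUSAR definition and can remove the expectedness assessment from a serious reaction in which the study drug may be involved

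*Protocol article*

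**What the plan says.** Under Adverse events, the protocol article describes a SUSAR as "an adverse drug reaction that is of a nature or a severity inconsistent with the applicable product information". The next sentence draws a conclusion from this: "Transfusion-related side effects will therefore not be declared as SUSAR". The text shown does not define the excluded group, sets no limit of severity, and gives no test for attributing a reaction to the platelets rather than to the study drug.

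Every patient receives blinded study drug or placebo and then platelets. On the interval between them the article makes these statements:

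- Experimental intervention: "a minimum waiting period of 10 min should be met whenever possible", followed by "A waiting period of 20–30 min would be ideal".
- Adherence to intervention protocols: the study medication "should be given at least 5 min before giving platelets".

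More platelets may follow in the 48-hour window; a single dose of drug is held to be enough "also in cases where further thrombocyte transfusions are needed".

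Table 3, which lists the 48-hour follow-up data, has one item that names AEs and SAEs: "Transfusion-related side effects (AE, SAE, see 3.7". Thromboembolic events and recurrent bleeding have items of their own.

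**The concern.** Whether a reaction is a SUSAR depends on three things: whether it is serious, whether the study drug may have caused it, and whether it is unexpected against that drug's product information. The label transfusion-related settles none of them. A categorical exemption by label therefore replaces the assessment it claims to rest on.

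This matters because the drug is used outside its registered indications (Background and rationale; Relevant concomitant care needs), and patients known to have the registered conditions are excluded (Exclusion criteria). A check of whether a serious reaction fits the existing product information is thus a real safeguard while patients are being enrolled.

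**Working it through.** No arithmetic applies: the rule depends on no error rate, effect size or sample size, and the plan gives no figure to reproduce. The check sets the passages side by side.

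**Step 1. When does the sentence change anything?** Apply the plan's own definition to three kinds of serious reaction.

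| Reaction | SUSAR by the definition? | Effect of the exempting sentence |
|---|---|---|
| Caused by the platelets alone | No, not a reaction to the study drug | None |
| Study drug may be involved; nature and severity fit the product information | No, expected | None |
| Study drug may be involved; nature or severity does not fit | Yes | Removes SUSAR status if labelled transfusion-related |

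The sentence is redundant in the first two rows. It has effect only in the third, where it is wrong.

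**Step 2. Can a third-row reaction receive the label?** Four features of the plan make this possible.

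- The stated intervals from drug to platelets are at least 5 min in one section, and a minimum of 10 min (ideally 20–30 min) in another. The two minimum intervals contradict each other and must be reconciled. On either, the products are given minutes apart.
- Further transfusions may follow within 48 hours.
- Staff watch for one list of allergic-type signs (skin, airway, shock, breathlessness) that is not divided by product. The study drug is itself plasma-derived (Experimental intervention).
- The only Table 3 item that names AEs and SAEs carries the transfusion-related heading.

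**Step 3. What still happens to such a reaction?**

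- Onset time, intensity and relation to the study treatment are recorded (Adverse events).
- All AEs and SAEs are collected and investigated (Safety), and SAEs are entered daily on the electronic case report form (Serious adverse reactions).
- An SAE leads to unblinding of that patient (Blinding).
- SAEs and SUSARs share one reporting clock: 7 days if fatal, otherwise 15 days (Serious adverse reactions).
- The safety analysis covers "number of SAE by severity grade, transfusion-related side effects, recurrent bleeding and the number of thromboembolic events within 48 h".

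**Step 4. What is left uncovered?**

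- *Expectedness.* In the text shown, SUSAR classification is the only step that compares a reaction with the product information. A reaction exempted by label skips it.
- *Prolonged hospitalisation.* The plan removes this criterion from its SAE definition. A reaction serious on that ground alone does not get the SAE handling in step 3. The text does not say whether the removal also governs what counts as serious for a SUSAR.

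**The case against.** The strongest reply is that little is lost in practice. A serious reaction denied the SUSAR label is still an SAE, so it is unblinded and reported just as fast. Both arms receive platelets, so drug reactions filed under the transfusion heading would tend to show as an excess in the active arm. Table 3 is not the only route for recording events, and its reference to a section 3.7 points to a fuller document that may define the term. The sentence may also be meant only for reactions caused by the blood product.

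Most of this stands, and it rules out several stronger inferences a reader might draw:

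- *That expedited reporting is lost.* It is not, because the clock is the same for SAEs and SUSARs.
- *That reported drug reactions are biased downward.* This is not shown, because these events are analysed and the randomised comparison does not depend on attribution.
- *That drug and platelets cause the same reactions.* No section says so. It is a plausible inference from the single list of signs and the drug's plasma origin.
- *That a given share of drug reactions would be mislabelled.* The documents give no onset times or reaction rates, so any percentage would rest on an invented distribution.
- *That the safety analysis should list non-serious allergic reactions.* That is detail the Statistics section leaves to the analysis plan.

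Two parts of the reply do not succeed. If the sentence covers only reactions caused by the blood product, it is unnecessary (first row of the table), and its wording does not limit it in that way. Recording relation to the study treatment does not clearly separate the products either, since Experimental intervention describes the medication as drug or placebo together with platelets. Even a clear causality entry would not override a categorical exemption.

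**Conclusion.** The concern holds in a limited form. The exemption is a stated rule that does not follow from the definition it is drawn from, and the only reactions it affects are those that should be assessed. The consequence is loss of SUSAR status, and with it of the expectedness assessment, for a serious reaction in which the study drug may be involved. For events serious only through prolonged hospitalisation, the SAE back-stop is missing too. Recording, unblinding, reporting speed and analysis of the remaining SAEs are intact.

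No number can be put on how often this would occur. The conclusion assumes that the label can attach to a reaction that is not purely due to the platelets, which the short interval and the Table 3 heading make possible but do not prove. It also assumes that some serious reactions would be unlisted, or more severe than listed; the product information is not shown. The point is worth correcting because the rule is wrong as written and the correction is cheap.

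**What to change.** - Delete the blanket sentence under Adverse events.
- State instead that each serious acute reaction is judged for causality separately for study drug and for platelets, and for expectedness against the study drug's product information. A reaction is exempt from SUSAR assessment only where a causal role of the study drug has been judged excluded.
- Relabel the Table 3 item so that it covers reactions to study drug and/or transfusion.
- Say whether the removed hospitalisation criterion also applies to seriousness for a SUSAR; deleting the sentence does not settle this.
- Reconcile the two minimum intervals between study drug and platelets.

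The cost is a wording change, one relabelled case report form item and a second causality entry. The downside is that a few more reactions go through SUSAR assessment.

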#### Laboratory parameters

Blood counts and global tests for coagulation, clinical chemistry biomarkers, vWF and FVIII levels and haemoglobin concentration will be analysed. Blood samples will be drawn during regular time points on the intensive care unit (e.g. 6 a.m.) except for the global platelet function analysis (VerifyNow®), which will be analysed right before the first study-specific platelet transfusion and 30–60 min after administration of the study drug and platelets.

#### Vital signs

Vital signs are continually measured at the ICU and recorded in the clinical IT system. The vital parameters include blood pressure, pulse, SpO_2_, ScvO_2_, SvO_2_ and respiratory rate. Also, the lowest temperature measured before ICU admission and again during the 2-day observation period and the fluid balance will be recorded.

## Definitions/conditions

### Inclusion criteria

Adult medical and surgical patients admitted to the ICU who need platelet transfusion with or without severe bleeding (i.e. needing transfusion of at least 2 ECs) will be included.

### Exclusion criteria

#### vWF/VIII concentrate given before study inclusion

Patients receiving factor VIII/vWF concentrate within 48 h (roughly four half-lives of factor VIII/vWF) before inclusion in the study (Haemate ®, Wilate ®) will not be included in the study as data collected from these patients might jeopardise the results.

#### Pregnancy/breastfeeding

Due to alterations in the overall coagulation abilities during pregnancy and lack of experience regarding the treatment during pregnancy and breastfeeding, these patients will be excluded. Moreover, postpartum haemorrhage is mostly managed following specific treatment protocols.

#### Participation in another study with investigational product

For security reasons, these patients will not be included in our study.

#### Overt DIC

Overt DIC for any reason (including trauma-induced DIC) will lead to the affection of the blood’s ability to clot and stop bleeding. Therefore, these patients will also be excluded from our study.

#### Pre-existing thrombocyte/vWF disorders

Patients suffering from innate or acquired platelet disorder (i.e. HIT, TTP, HUS, ITP, sepsis, haemato-oncological disease, other hereditary thrombocytopathies)—with the exception of prior treatment with single or dual antiplatelet agents—or disease affecting vWF (i.e. von Willebrand disease, haemophilia A) will be excluded from the study in order to be able to reliably assess the effect of vWF when added to platelets.

Hypersensitivity to the active substances is defined as a known allergy to vWF or a substance contained in the placebo.

### Primary outcome measure

#### Number of transfusions

This is the number of blood products (fresh frozen plasma (FFP), RBCs, platelet concentrates) transfused within the first 48 h after study allocation in both groups (Tables 2 and 3).

**Table 2 Tab2:** Baseline data assessed upon study inclusion (data prior/upon admission to ICU) to be documented *before* administration of the study drug

	***Metavision®***	***RedCap®***
Informed consent or statement of an independent physician		X
Randomisation, assignment of the group		X
Demographics^a^	X	
Admission diagnosis		X
Past medical history		X
Relevant medication prior to bleeding (1 month)^b^		X
Type of admission (medical, surgical)		X
SAPS II	X	
SOFA score	X	
Type of surgery (if applicable)		X
Cause of bleeding		X
Reason for thrombocyte transfusion		X
Amount of blood loss prior to ICU admission	X	
Vital parameters^c^	X	
Lowest temperature measured^d^	X	
Lowest temperature measured		
Fluid balance^e^	X	
Full blood count and chemogram^f^	X	
Coagulation laboratory^g^	X	
Platelets function analysis (VerifyNow® ADP test) *before* administration of the study drug		X
Number of given RBCs	X	
Number of given FFPs	X	
Number of given platelet concentrates	X	
Amount of prothromblex	X	
Amount of tranexamic acid	X	
Amount of fibrinogen	X	
Name/amount of other given coagulation products^h^	X	
Transfusion-related side effects (AE, SAE)	X	
Thromboembolic events	X	

^a^Age, sex, BMI, height, social security number (identification log only)

^b^NOACs, antiplatelet agents and oral anticoagulation such as Marcumar® (phenprocoumon), Eliquis® (apixaban), Lixiana® (edoxaban), Xarelto® (rivaroxabam), Pradaxa® (dabigatran), Aspirin ® (ASS) and Plavix® (clopidogrel)

^c^Blood pressure, pulse, SpO_2_, ScvO_2_, SvO_2_ and respiratory rate

^d^Lowest temperature measured before ICU admission

^e^In surgical patients from anaesthesia induction until ICU admission; non-surgical patients: fluid balance (if available) upon ICU admission

^f^Hemoglobin, leucocytes, erythrocites, haematocrit, mean corpuscular volume (MCV), mean corpuscular haemoglobin (MCH), mean corpuscular haemoglobin concentration (MCHC), red cell distribution width (RDW), thrombocytes, quick, international normalised ratio (INR), activated partial thromboplastin time (APTT), thrombin time 1 (TZ1), fibrinogen and β-subunit of human chorionic gonadotropin (βHCG) in female study participants of reproductive age < 45 years

^g^Including von Willebrand factor ristocetin cofactor (VWF:Rco); factors II, V, and VII; INR; and platelets count and level of thrombin

^h^Beriplex, Cyklokapron, Konakion, Kyberin, Fibrogammin, NovoSeven, ionised calcium, etc. (see Additional file 1: Table S1)

**Table 3 Tab3:** ICU follow-up data to be assessed within the 48-hour study period beginning at study drug administration

	***Metavision®***	RedCap®
Administration of study medication (or placebo)		
Platelet function analysis (VerifyNow® ADP test) 30–60 min after administration of study drug		X
Check if informed consent is possible		X
Amount of blood loss since drug administration		X
Cause of bleeding (if occurred)		X
SOFA score	X	
Vital parameters^a^	X	
Lowest temperature measured^b^		X
Acidosis occurred (pH < 7.35)		X
Duration of acidosis		X
Full blood count^c^	X	
Coagulation laboratory^d^	X	
ROTEM	X	
Level of vWF and FVIII	X	
Haemoglobin concentration	X	
Fluid balance^e^	X	
Number of given RBCs	X	
Number of given FFPs	X	
Number of given platelet concentrates	X	
Amount of Prothromblex after study intervention	X	
Amount of tranexam acid after study intervention	X	
Amount of fibrinogen after study intervention	X	
Name/amount of other given coagulation products^f^	X	
Number of revision surgery for haemorrhage control		X
Transfusion-related side effects (AE, SAE, see 3.7)^g^		X
Thromboembolic events		X
Any recurrent bleeding such as cerebral haemorrhage, DIC		X

^a^Blood pressure, pulse, SpO_2_, ScvO_2_, SvO_2_ and respiratory rate

^b^Lowest temperature measured since ICU admission

^c^Hemoglobin, leucocytes, erythrocites, haematocrit, mean corpuscular volume (MCV), mean corpuscular haemoglobin (MCH), mean corpuscular haemoglobin concentration (MCHC), red cell distribution width (RDW), thrombocytes, quick, international normalised ratio (INR), activated partial thromboplastin time (APTT), thrombin time 1 (TZ1), and fibrinogen^d^ including factors II, V and VII; INR; platelets count; and level of thrombin

^e^Since ICU admission until 48 h after the study drug administration

^f^Beriplex, Cyklokapron, Konakion, Kyberin, Fibrogammin, NovoSeven, ionised calcium, etc. (see above)

^g^48-h observation period

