### Determination of sample size

A total of 120 (each group 60) patients are needed to detect a 50% reduction of the number of blood products subsequently transfused within two days in patients with Wilate® compared to placebo. The sample size is calculated for a power of 80 % and a significance level of 5% for an estimate of the treatment effect evaluated with a negative binomial regression. To improve the precision of the treatment effect, the following covariates will be included: blood loss, number of blood products transfused within 12 h before administration of the study drug, anticoagulants administered 7 days before, the site of bleeding and the level of thrombocytes at baseline. The sample size calculation is based on a simulation applying resampling techniques on historical clinical data of 150 USB patients that meet the inclusion criteria.

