##### Amount of blood loss

The difference in blood loss in ml within 2 days after platelet transfusion between the study groups will be analysed similarly to the primary endpoint (number of blood products administrated).

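### The primary count is defined in incompatible ways, and on its literal definition it includes the platelet concentrate given as study treatment, so a true 50% reduction cannot appear as 50%

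*Protocol article*

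**What the plan says.** The protocol article describes the primary count in several places, and they do not agree.

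- **Outcome measures, Primary outcome measure** (and the abstract): FFP and RBC only. Platelets are absent and this section gives no time window.
- **Definitions/conditions, Number of transfusions**: FFP, RBC and platelets, "platelet concentrates) transfused within the first 48 h after study allocation in both groups". No unit is excluded.
- **Primary analysis**: platelets, RBC and FFP administered, again with no exclusion.
- **Statistics, Hypothesis**: further products of all three kinds in the 48 h after treatment.
- **Determination of sample size** sets the target for later units over a 48-hour period: "A total of 120 (each group 60) patients are needed to detect a 50% reduction of the number of blood products subsequently transfused within two" […].

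Platelets are also part of the allocated treatment. Study period overview defines the arms as platelet transfusion with vWF or with placebo. Under Experimental intervention, "Additionally, one platelet concentrate provided by the blood bank of the University Hospital of Basel will be ordered" with the study package, while the dosing paragraph gives the drug "in combination with one or two platelet concentrates". Laboratory parameters refers to a first study-specific platelet transfusion. The dosing paragraph and Adherence to intervention protocols both place the drug before the platelets.

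The 48-hour window also has more than one start. It is allocation in Number of transfusions and Number of platelet transfusions. It is the study drug or treatment in the list of secondary outcomes, in the statistical hypothesis and in Table 3 ("ICU follow-up data to be assessed within the 48-hour study period beginning at study drug administration"). For blood loss it is "within 2 days after platelet transfusion".

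**The concern.** A unit that the protocol gives to everyone after allocation carries no information on whether the drug reduces later transfusion. Read literally, the operational definition scores that unit as outcome in both arms. A constant added to both arms pulls a ratio towards 1, so the quantity estimated is not the one for which the 50% target was set. It also removes all zeros from the count, which a negative binomial model does not expect.

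At stake are the size of the primary effect estimate, its comparison with the planned 50%, and the error rate of the primary test. If the definition stays open, the choice between a count with the study concentrate, one without it, and one without any platelets could be made after the data are seen.

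**Working it through.** **Inputs from the article (Determination of sample size).** 60 per arm, a 50% reduction (rate ratio 0.5), and "The sample size is calculated for a power of 80 % and a significance level of 5% for an estimate of the treatment effect" from negative binomial regression. Sidedness is not stated; two-sided is assumed. The control mean and the dispersion are not given; they lie in the 150 historical patients that were resampled.

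**The plan's own figure.** The total of 120 cannot be reproduced without those two values. What can be found is which pairs of control mean m and dispersion a would give 60 per arm in an unadjusted two-group comparison:

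n per arm = (1.960 + 0.842)² × [1/m + 1/(0.5m) + 2a] / (ln 0.5)²

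Setting n = 60 gives 3/m + 2a = 3.673, so a = 1.09, 1.46 and 1.59 for m = 2, 4 and 6. These pairs are assumptions, not the trial's values.

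**Step 1: shrinkage of the ratio.** Let m be the mean number of further products in the control arm. With a true ratio of 0.5 and one study concentrate per patient, the expected ratio of total counts is (0.5m + 1)/(m + 1). This needs no distributional model.

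| m | Expected ratio | Apparent reduction |
|---|---|---|
| 1 | 1.5/2 = 0.750 | 25% |
| 2 | 2/3 = 0.667 | 33% |
| 4 | 3/5 = 0.600 | 40% |
| 6 | 4/7 = 0.571 | 43% |
| 8 | 5/9 = 0.556 | 44% |

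With two fixed units the ratio is (0.5m + 2)/(m + 2): 0.75, 0.667 and 0.625 for m = 2, 4 and 6.

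The secondary platelet count has the same fault. There m is the mean of further platelet units alone, which cannot exceed the mean for all products, so the shrinkage is at least as large.

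**Step 2: the model-based test.** Trials of 60 per arm were simulated with the back-solved dispersion, a maximum-likelihood negative binomial fit and a Wald test, without covariates (6,000 null runs and 2,000 runs at ratio 0.5 per row).

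| m | a | Type I error, unit excluded | Type I error, unit counted | Power, unit excluded | Power, unit counted |
|---|---|---|---|---|---|
| 0.9 | 0.17 | 0.055 | 0.007 | 0.82 | 0.45 |
| 1.2 | 0.59 | 0.054 | 0.036 | 0.80 | 0.67 |
| 1.5 | 0.84 | 0.060 | 0.065 | 0.81 | 0.79 |
| 2 | 1.09 | 0.054 | 0.074 | 0.81 | 0.83 |
| 4 | 1.46 | 0.054 | 0.101 | 0.81 | 0.87 |
| 6 | 1.59 | 0.052 | 0.099 | 0.81 | 0.86 |

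For control means of about 2 or more at this dispersion, type I error with the unit counted is about 0.07 to 0.11 across runs, mostly near 0.09 to 0.10. Other settings give:

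- Two prognostic covariates in the model: 0.084 to 0.092 with the unit, 0.060 to 0.066 without it.
- Low dispersion (m = 4, a = 0.3): 0.059 with the unit, 0.053 without it, so almost no change.
- Below about 1.3 further products: the test is conservative and loses power.
- Robust variance with the unit counted: type I error about 0.055 to 0.07 and power about 0.79 to 0.83. The ratio remains shrunken.

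**Step 3: the clocks.** A window that opens at allocation and one that opens at study drug both contain the study concentrate, because the platelets follow the drug. The clocks therefore cause neither effect above. The covariate "number of blood products transfused within 12 h before administration of the study drug" ends at the drug, so a unit given between allocation and drug would fall in both covariate and outcome. Table 1 places randomisation and study medication both at time 0, so few units should be affected.

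**The case against.** The strongest reply is that the article does not settle that the study concentrate counts. The hypothesis and the sample size section point to excluding it, and under the outcome list no platelet unit counts, so the problem disappears. That stands as far as it goes: a reader might infer that the plan definitely scores the study concentrate as outcome, and the documents support only that its literal operational definition and its primary analysis do so. But the reply rests on other passages that contradict those two, and this contradiction is the defect.

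A reader might also infer that the negative binomial test is anti-conservative outright. The documents do not support that. They give no control mean or dispersion, and eligibility covers patients with or without severe bleeding, so a low mean cannot be ruled out; there the direction reverses. The back-solved dispersion also treats the sample size as unadjusted, whereas the plan resampled historical data for a model with five covariates.

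Two further limits stand. A fixed unit leaves the difference in means unchanged; the harm is to the ratio and to the model-based error rate. Poor coverage of 0.5 by confidence intervals for the total-count ratio would mostly restate the shrinkage, so it is not counted here as a separate fault. Nor do the conflicting clocks share the blame, and the one for blood loss concerns a secondary outcome.

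**Conclusion.** The point holds as a conflict of definition in the primary outcome that should be resolved before analysis. If the study concentrate is counted, the shrinkage is certain: a true 50% reduction in further products appears as 25% to 44% for assumed control means of 1 to 8 with one fixed unit. The estimate then does not correspond to the planned 50%, unless the historical resampling counted that unit too, which the article does not say.

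The effect on the test is conditional. With the dispersion implied by 60 per arm, type I error is about 0.07 to 0.11 for control means of about 2 or more, changes little at low dispersion, and falls below 5% with reduced power for means below about 1.3. The differing clocks are real but minor.

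**What to change.** 1. Use one definition in the outcome list and abstract, the definitions section, the hypothesis, the sample size section and the primary analysis: further RBC, platelet and FFP units within 48 h, excluding the platelet concentrate(s) given as part of study treatment.
2. Reconcile the two statements under Experimental intervention on whether study treatment comprises one concentrate or one or two, and then state which units are excluded. Whether a second concentrate counts as outcome should follow from that reconciliation.
3. Apply the same rule to the secondary platelet count.
4. Name one time zero, for example the start of study drug or placebo as in Table 3, with allocation time for a randomised patient never dosed. End the 12-hour covariate window there.
5. Confirm that the resampling of the 150 historical patients used this same count, or rerun it.
6. If the study unit is kept in the count, restate the target ratio and use a robust variance or a permutation test.

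The cost is an amendment of wording in the protocol and analysis plan, a time-stamp filter on transfusion data that Table 3 already collects, and at most one rerun of the sample size simulation.
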